#### Secondary outcomes

Secondary outcomes will include 7-day point-prevalence abstinence (at all subsequent checkups; biochemically validated at weeks 12, 24, 36, 48, and 60). As a secondary goal, this study will analyze the harm-reduction effect of e-cigarettes and nicotine pouches, as well as the analysis of adverse events.

### Statistical analysis

To provide a summary position of the important variables of the population under clinical trial, a univariate analysis will be employed for data analysis and reporting. To examine the cross-relationship and association between selected variables, bivariate analysis and cross tabs will be used. Univariate data analysis is relevant and provides easy to understand information for focusing on a given variable at a time. The bivariate data analysis is helpful in examining the relationship and association between selected variables based on the understanding from previous studies or the theory. The differences in intervention indicators between the control and the treatment groups will be evaluated with the simple *t*-test and variance analysis.

The information obtained from the baseline survey will help in the planning (refine targeting, indicators to monitor), recommendations toward study design, implementation, and fine-tuning of the intervention objectives, backed by evidence-based research. However, the real execution of true experiment in the field is almost impossible due to heterogeneity of the beneficiaries. Therefore, we propose an alternate but similar approach, i.e., quasi-experimental difference in difference (DID) design, which is a close form of experimental research, widely used in the social sciences. The second-best option would be propensity score matching (PMS) technique to estimate the average treatment effect of the interventions.

The basic technique for taking DID for average and percentages of project is also referred to as the double difference evaluation design. It can measure change in outcome variables over time and across groups (beneficiaries compared with non-beneficiaries), a standard practice to ascertain and establish the attribution of a program in terms of outcome indicators. The sample requirements for a DID design are smaller than other impact evaluation designs. Table 2 and its accompanying chart illustrate how the DID estimator will measure the treatment effects of the program. In order to mitigate attrition bias, the analysis incorporates outcome data from all participants, irrespective of their adherence to the study protocol. This approach, known as “intention-to-treat” analysis, encompasses both randomized participants, serving as the recommended strategy for analysis. Additionally, the protocol must outline the intended approach for managing missing data during analysis. It should articulate the proposed methods for estimating missing outcome data, such as imputation, along with specifications regarding the variables employed in this process, if possible.

**Table 2 Tab2:** The double difference design to measure treatment effect

	Baseline value of indicator	Follow-up value of indicator	Difference over time
Beneficiary group (intervention)	a	c	c–a
Non-beneficiary	B	d	d–b
(comparison)			
Difference over group	a–b	c–d	DID (treatment effect) = (d–b)–(c–a)
			or
			(a–b)–(c–d)

Depending upon the measurement scale of each indicator, the cells (a, b, c, and d) in the table can be primary and secondary outcomes indicators

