**Method:**

Keeping in view the study objectives, a sample size of 600 participants will be sufficient to assess the effectiveness of e-cigarettes and nicotine pouches for smoking cessation in Pakistan. Of these, 200 participants each will receive e-cigarettes and nicotine pouches along with basic care counselling, while the remaining 200 participants will only receive basic care counselling for 48 weeks. The association of participants’ characteristics with smoking and health status will be based on the bivariate and multivariate analysis. The simple *t*-test and variance analysis will assess the differences in intervention indicators between the control and treatment groups. For the inferential analysis, the average treatment impact will be based on the quasi-experimental techniques such as difference in difference (DID) or propensity score matching (PMS).

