### Study design

After the screening of the participants, this study will conduct a baseline survey to evaluate smoking status, smoking behavior, sociodemographic characteristics, health status, economic barriers, and motivation to stop smoking before the intervention and try to make a balance randomization between the control and the treatment groups. After completing the baseline survey, the three-arm study design would randomize 600 participants into three groups.E-cigarette: The 200 participants will receive e-cigarettes along with basic care counselling.Nicotine pouches: The 200 participants will receive nicotine pouches along with basic care counselling.Basic care counselling: The 200 participants will receive basic care counselling.

Four basic care counselling sessions will be held over the course of 48 weeks with the supply of e-cigarettes and nicotine pouches. These e-cigarettes and nicotine pouches will be provided in line with the indicated tastes and flavors. Every 12 weeks, a standard care counselling session will be offered, followed by a study visit to track any alterations in the user’s physical or mental health as well as any side effects from using nicotine pouches or e-cigarettes. All participants will complete a follow-up survey at 60 weeks. However, the provision of e-cigarettes and nicotine pouches will be stopped after the first 48 weeks.

The remaining 12 weeks will be followed without providing any e-cigarettes or nicotine pouches. The participants must buy these items on their own. The overall five follow-ups will be conducted over the course of 60 weeks. Of these, four follow-ups will be during the period in which the participants received interventions, and one follow-up will be post-intervention period of 48 weeks. Additionally, a flowchart depicting the unified requirements of reporting trial is shown in Figs. 1 and 2 along with the explanation of the participants’ research schedule.

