#### Data cleaning and coding

Capitalizing on our experience in conducting and managing field surveys, we will develop a data coding strategy to ensure the following:◦ Each respondent/interviewee selected will be assigned a unique identifier.◦ Each enumerator and supervisor will have a unique code that will be recorded on all questionnaires completed by a given team. This will ensure the quality assurance of data management by evaluating the performance of everyone separately.◦ All geographical denominations will have a unique location code in the database.◦ Assign variable names, values, and labels to clean the database.

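### For the abstinence primary outcome, the stated group comparisons (simple test and difference-in-difference) make no use of the recorded baseline predictors; a prespecified adjusted model would be modestly more precise

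*Protocol article*

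**What the plan says.** All references are to the protocol article.

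- **Group comparison.** Statistical analysis: "The differences in intervention indicators between the control and the treatment groups will be evaluated with the simple" t-test and variance analysis. The Abstract (Method) says the same. No covariates are named.
- **Treatment effect.** Statistical analysis proposes a "quasi-experimental difference in difference (DID) design, which is a close form of experimental research". Of matching it says: "The second-best option would be propensity score matching (PMS) technique to estimate the average treatment effect of the interventions". The note under Table 2 lets the cells of the DID table hold primary or secondary outcomes.
- **Multivariate analysis.** It appears in the Abstract (Method), for another purpose: "The association of participants’ characteristics with smoking and health status will be based on the bivariate and multivariate analysis".
- **Outcome.** Primary outcomes lists cigarettes per day and 7-day point abstinence at weeks 24 and 48, the latter validated by exhaled CO below 10 ppm.
- **Data available.** Study design plans a "baseline survey to evaluate smoking status, smoking behavior, sociodemographic characteristics, health status, economic barriers, and motivation to stop smoking before the intervention", and says that balance between the arms will be attempted. Recruitment takes place in two districts (Recruitment strategies), and Data cleaning and coding adds: "All geographical denominations will have a unique location code in the database".

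**The concern.** Abstinence is a binary primary outcome with no informative baseline value of its own, because everyone is a smoker at entry. Any gain in precision has to come from other baseline variables. The article collects such variables before randomisation but names no dependable analysis of abstinence that uses them.

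The article justifies DID by the heterogeneity of participants. For cigarettes per day, DID does bring in the baseline value. For abstinence it does nothing about heterogeneity.

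At stake are some power in a comparison already below the article's own 80% target at its chosen rates, and protection against chance imbalance in, say, motivation or smoking level. The validity of the trial is not at stake.

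**Working it through.** **1. The article's own sample size.** Inputs from Table 1: p1 = 0.18, p2 = 0.09, Z = 1.96 and 0.84. With the printed formula:

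n = (1.96 + 0.84)² × (0.18×0.82 + 0.09×0.91) / 0.09² = 7.84 × 0.2295 / 0.0081 = 222.13.

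This reproduces the stated 222.

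**2. Power at the planned 200 per arm.** The standard error is √(0.2295/200) = 0.0339, and 0.09/0.0339 − 1.96 = 0.70, which gives 75.7% power. With a pooled variance under the null it is 75.2%.

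**3. DID on abstinence.** Inclusion criteria require more than 10 cigarettes a day at enrolment, so baseline abstinence is 0 in each arm: a = b = 0 in Table 2. The printed estimator (d−b) − (c−a) becomes d − c, and the alternative (a−b) − (c−d) also becomes d − c. Apart from sign this is the unadjusted follow-up difference c − d. DID and the simple test thus target the same unadjusted quantity.

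**4. What adjustment could add.** The article gives no prognostic strength, so a range is assumed. With a share R² of outcome variance explained, the effective size is 200/(1−R²):

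| R² (assumed) | Effective n per arm | Power (pooled) |
|---|---|---|
| 0 | 200.0 | 75.2% |
| 2% | 204.1 | 76.0% |
| 5% | 210.5 | 77.3% |
| 10% | 222.2 | 79.5% |

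To offset 200 against 222 needs R² = 1 − 200/222.13 = 10.0%.

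**5. Simulation with one baseline score.** Settings: 200 per arm, marginal rates 9% and 18%, two-sided 0.05.

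| AUC of score (assumed) | Unadjusted | Adjusted | Adjusted method |
|---|---|---|---|
| 0.50 | 76.0% | 75.5% | logistic |
| 0.58 | 76.3% | 76.0% | logistic |
| 0.64 | 75.3% | 76.3% | logistic |
| 0.69 | 76.6% | 78.4% | logistic |
| 0.75 | 76.0% | 81.0% | logistic |
| 0.50 | 76.3% | 76.4% | standardised risk difference |
| 0.64 | 75.2% | 76.4% | standardised risk difference |
| 0.71 | 75.1% | 78.9% | standardised risk difference |
| 0.75 | 75.5% | 80.0% | standardised risk difference |

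The logistic rows use 6,000 trials each and the risk-difference rows 4,000. Monte Carlo standard errors are about √(0.76×0.24/6000) = 0.6 and √(0.76×0.24/4000) = 0.7 points, so the spread in the unadjusted column is noise. Null rejection of the adjusted risk-difference test was 4.2% to 5.2%. In the logistic simulation, an AUC of 0.75 corresponds to R² of about 9% in the control arm and 13% in the treated arm.

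**6. Simulation with six estimated covariates.** This is closer to the model proposed below. With useless covariates, power went from 76.1% to 76.0%. With prognostic ones it went from about 75–78% to 76–81%. Null rejection was 4.9% to 6.0% adjusted, against 4.6% to 5.6% unadjusted.

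**7. Room for covariates.** Expected quitters per pairwise comparison: 200×0.18 + 200×0.09 = 54. Six terms leave 54/6 = 9 events per term.

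**The case against.** **The quoted sentence is not the stated effect analysis.** It closes a descriptive paragraph; DID and matching are named separately for the treatment effect. This stands: a reader should not infer that a t-test is the only planned analysis. The point survives because DID equals the same unadjusted difference for abstinence. Matching does use covariates, but it is only second choice, and it may drop randomised participants, which sits poorly with the intention-to-treat commitment in the same section.

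**Scope.** An unadjusted randomised comparison is valid, and a covariate list commonly sits in an analysis plan that is not shown here. Also true, so the missing list is not the finding. The finding is that the estimators which the article does name suit this outcome poorly.

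**Predictor strength.** A reader might suppose the recorded variables are strong predictors. No figure in the article supports that. Eligibility also narrows the range: all smoke more than 10 a day, are willing to stop, and are motivated to set a quit date within two weeks. The weaker rows of the table may be the more realistic ones.

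**Standard errors.** A reader might infer that the unadjusted standard error is too wide. That would follow only if allocation is in fact balanced on predictors. Study design says only that balance will be attempted, and no balancing or stratification factor is stated. District is an available covariate, not one that the stated design requires.

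**Sample size.** The shortfall against 222 is a separate matter and applies to the rates that the article adopted. The other three pairs in Table 1 give 87% power or more at 200 per arm. Data collection plan: retention also mentions enrolling above the optimum, by an unstated amount.

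**Conclusion.** The point holds as an efficiency concern. For abstinence, neither the simple test nor DID uses the recorded predictors, and the fallback is not a dependable substitute. The stated comparison is valid but less precise than it need be.

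The size is about 0 to 5 power points on a base of about 75–76%. This rests on three assumptions: 18% versus 9% applies to 7-day validated abstinence (Table 1 does not name its outcome, and the article describes the source trial's aim as one-year sustained abstinence); 200 per arm contribute outcomes; and predictor strength lies in the assumed range.

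It would be tempting to conclude that adjustment cures the under-sizing. It reaches about 80% only at the strongest assumed score, so that conclusion is not supported.

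**What to change.** For CO-validated abstinence at weeks 24 and 48, make the main comparison of each product with counselling a prespecified logistic model containing:

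- arm;
- a short fixed list of recorded baseline variables, for example cigarettes per day, motivation, age, sex and district;
- any factor actually used to balance the randomisation.

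Keep to about five or six covariate terms in all. Report the standardised risk difference with a robust standard error, and keep the unadjusted difference as a supporting analysis. State in the text that DID for abstinence equals that unadjusted difference.

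The cost is wording; no new data or participants are needed. The covariates must be fixed before outcome data are seen, and nothing is gained if they turn out not to be prognostic. The mismatch between 200 and 222 per group must still be resolved separately.

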Based on the aforementioned formulas, from Hajek et al. [50], Smith et al. [12], Rigotti et al. [14], and Caponnetto et al. [16] derived 222, 49, 86, and 163 for single group respectively. According to acceptable norms and standards, the selected sample should represent the population. By the safe decision and following the abovementioned procedure, this study proposes a sample size of 600 participants, which will be randomly divided into three groups as follows:E-cigarette: The 200 participants will receive e-cigarettes along with basic care counselling.Nicotine pouches: The 200 participants will receive nicotine pouches along with basic care counselling.Basic care counselling: The 200 participants will receive basic care counselling.

Under the Lead Researcher [name], ARI team will conduct interview of participants and assign and unique ID to each potential participant at the screening stage. After that, the lead research Dr. [name] will generate the allocation sequence and will assign participants to interventions by using STATA software for the randomization.

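### A randomised trial is analysed under a quasi-experimental label for a mistaken reason, and the choice between difference-in-difference and propensity score matching is left open

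*Protocol article*

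**What the plan says.** Allocation is plainly randomised. Under Study design, "the three-arm study design would randomize 600 participants into three groups", with 200 in each. Under Sampling strategy and sample selection, the lead researcher generates the sequence and "will assign participants to interventions by using STATA software for the randomization".

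The Statistical analysis section then states: "However, the real execution of true experiment in the field is almost impossible due to heterogeneity of the beneficiaries". It continues: "Therefore, we propose an alternate but similar approach, i.e., quasi-experimental difference in difference (DID) design". PSM follows as the fallback: "The second-best option would be propensity score matching (PMS) technique to estimate the average treatment effect of the interventions". The same section also assigns the comparison of arms to simpler tests: "The differences in intervention indicators between the control and the treatment groups will be evaluated with the simple *t*-test and variance analysis".

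The abstract's Method paragraph does not rank the two main methods. There, "the average treatment impact will be based on the quasi-experimental techniques such as difference in difference (DID) or propensity score matching (PMS").

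After introducing DID, the Statistical analysis section commits to using outcome data from everyone whatever their adherence, and adds: "This approach, known as “intention-to-treat” analysis, encompasses both randomized participants, serving as the recommended strategy for analysis". Table 2 then gives the DID arithmetic.

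**The concern.** Two things are stated wrongly or fixed badly.

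First, the ground for leaving the experimental framework is an error. Differences between participants do not prevent a true experiment. Random allocation makes the arms comparable in expectation however varied the participants are. Calling the comparison quasi-experimental undersells evidence that the design protects.

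Second, the document does not settle on one estimator. The body ranks DID above PSM but says nothing about when PSM would replace it. The abstract offers either one as an example of a class of techniques. T-tests and analysis of variance stand beside them. With the headline effect open in this way, a reader of the results could not rule out that the method was picked after the data were seen.

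PSM is also the wrong tool for this purpose. It models how people came to receive treatment, and here allocation is fixed by design, so there is no selection to model.

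**Working it through.** **Inputs from the protocol article.** 200 per arm (Study design). Table 1 planning values: 18% against 9%, two-sided alpha 0.05, power 0.80. Every participant smokes more than 10 cigarettes a day at entry (Inclusion criteria). Primary outcomes are cigarettes per day and 7-day abstinence at weeks 24 and 48 (Primary outcomes). The document gives no baseline-to-follow-up correlation, matching algorithm, caliper or covariate list, so values for these below are assumptions.

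**1. The plan's own figure.** n = (1.96 + 0.84)² × [0.18 × 0.82 + 0.09 × 0.91] / (0.18 − 0.09)² = 7.84 × 0.2295 / 0.0081 = 222.1 per group, as in Table 1. This formula compares two follow-up proportions as randomised. It is not a DID or PSM calculation. At the 200 per arm actually chosen, power is 0.75 (pooled variance) or 0.76 (unpooled).

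**2. DID for abstinence.** Call the product arm's baseline and follow-up values a and c, and the counselling arm's b and d, as in Table 2. All participants smoke at entry, so a = b = 0. Table 2's expression (d − b) − (c − a) becomes d − c = 0.09 − 0.18 = −0.09. That is the simple risk difference in size, with its sign reversed by the way Table 2 orders the terms. Nobody with an outcome is excluded.

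**3. DID for cigarettes per day.** With equal variance at both times and correlation ρ, the variance of the between-arm difference, relative to using follow-up alone (= 1), is:
- DID: 2(1 − ρ)
- regression adjusted for baseline (ANCOVA): 1 − ρ²
- ratio of DID to ANCOVA: 2(1 − ρ) / [(1 − ρ)(1 + ρ)] = 2 / (1 + ρ)

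| Assumed ρ | DID | ANCOVA | Ratio |
|---|---|---|---|
| 0.3 | 1.40 | 0.91 | 1.54 |
| 0.5 | 1.00 | 0.75 | 1.33 |
| 0.7 | 0.60 | 0.51 | 1.18 |

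Equivalently, 200 per arm under DID is worth 200 × (1 + ρ)/2 = 130, 150 or 170 per arm under ANCOVA. Below ρ = 0.5, DID is less precise than ignoring baseline altogether.

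**4. PSM.** Greedy 1:1 matching of 200 against 200 randomised participants was simulated with 5, 10 or 20 independent normal covariates, 200 runs per setting. The last column is the pooled power for 18% against 9% at the mean number of pairs.

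| Caliper (SD of the logit) | Mean unmatched of 400 (5 / 10 / 20 covariates) | Power |
|---|---|---|
| none | 0 / 0 / 0 | 0.75 |
| 0.2 | 53 / 62 / 78 | 0.69 / 0.68 / 0.66 |
| 0.1 | 71 / 78 / 91 | 0.67 / 0.66 / 0.64 |
| 0.05 | 99 / 104 / 113 | 0.63 / 0.62 / 0.61 |

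With a caliper, the unmatched share runs from 53/400 = 13% to 113/400 = 28%. Without one it is 0%.

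In a separate simulation (10 covariates, caliper 0.2, ρ = 0.5, 600 replicates), the variance of the estimate was 0.0101 unadjusted, 0.0096 for DID, 0.0090 for PSM and 0.0075 for baseline-adjusted regression. PSM was therefore 0.0090/0.0075 = 1.20 times as variable as baseline adjustment, but no worse than the unadjusted comparison.

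**The case against.** A reader might infer that the planned analysis discards randomised participants, contradicts intention-to-treat and forfeits the protection of randomisation. The document does not support that.

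The first-choice method is DID. Applied to the arms as randomised, it uses everyone with baseline and follow-up data. The intention-to-treat statement sits in the same paragraph as the DID description, so as written the two go together. The parallel-trends assumption that DID needs holds in expectation because allocation is random. Change in smoking rate from baseline is itself a named primary outcome, so a difference in mean change is a natural estimate. Preferring ANCOVA is a gain in precision, not a correction of bias.

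The exclusion charge can apply only to PSM, and only if unmatched people are dropped or matching follows product use instead of assigned arm. The document states neither.

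The openness of the estimator can also be overstated. The body does rank the options, and a t-test on change scores gives the same estimate as DID. Matching variables, calipers and a fallback rule may reasonably be left to an analysis plan that is not shown.

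All of that stands. What it does not answer is the mistaken reason for calling a randomised comparison quasi-experimental, the lack of ranking in the abstract against the ranking in the body, and the naming of PSM as an effect estimator at all. These are things the document says, not details it omits.

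**Conclusion.** The point holds in a limited form and should be fixed. The rationale and label are wrong for an individually randomised trial, and the document leaves room to choose between DID and PSM after the results are known.

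The first-choice estimator is valid under randomisation, so the headline result is not invalidated, and this falls short of a fault that must be fixed before the trial can be relied on. For abstinence, DID costs nothing against the risk difference. For cigarettes per day, its variance is 18% to 54% larger than that of baseline-adjusted regression, assuming ρ between 0.7 and 0.3 and equal variances over time. The conflict between PSM and intention-to-treat is a risk and not a stated exclusion. Its size, from 0% to about 28% unmatched, depends wholly on assumed matching rules.

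**What to change.** - Delete the sentence saying that a true experiment is almost impossible, and the quasi-experimental label.
- State one intention-to-treat comparison of each product arm with counselling for each primary endpoint: a risk difference with 95% confidence interval for CO-verified abstinence, and linear regression of follow-up cigarettes per day on arm and baseline cigarettes per day.
- Remove PSM as an estimator of the treatment effect, or limit it to exploratory analyses by actual product use.
- Make the abstract's Method paragraph say the same as the body.

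The cost is rewording of the Statistical analysis section and the abstract. No new data are needed, but the change should be made before outcome data are analysed.

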#### Inclusion criteria

The potential participants for the trial will have to meet the following requirements.◦ Participants are at least 18 years old. Upper age limit is 65 years.◦ Smoke more than 10 combustible cigarettes a day at the time of study enrollment◦ Smoking cigarettes for at least a year◦ Participants are willing to stop combustible smoking.◦ Participants are ready to sign a written consent form.◦ There can only be one applicant per household.◦ Own a phone that supports text messaging

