#### Primary outcomes

The primary outcome will be long-term change in health status. The best proxy indication for demonstrating a reduction in toxin intake from tobacco smoking that is adequate to result in a clinically relevant long-term health benefit is unknown [59]. In the absence of more accurate health indicators, the change in smoking rate from baseline and the smoking cessation will be the primary outcomes. This study will evaluate the impact of e-cigarettes and nicotine pouches on cigarettes per day (CPD and smoking cessation (7-day point abstinence) at weeks 24 and 48 (the study period ends in 60 weeks. At 48 weeks, ARI will be ending the provision of the interventions). Self-reported point-prevalence abstinence in the previous week with biochemical validation will be exhaled carbon monoxide less than 10 parts per million (PPM).

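### The statement that difference-in-difference needs a smaller sample does not hold in general here: for abstinence it saves nothing, and for cigarettes per day it is never more precise than adjusting for baseline

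*Protocol article*

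**What the plan says.** The Study design section states that "the three-arm study design would randomize 600 participants into three groups", with 200 in each. The Primary outcomes section names CPD and "smoking cessation (7-day point abstinence) at weeks 24 and 48".

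The Statistical analysis section first says: "The differences in intervention indicators between the control and the treatment groups will be evaluated with the simple" *t*-test and variance analysis. For the treatment effect it proposes a "quasi-experimental difference in difference (DID) design, which is a close form of experimental research", with propensity score matching as second choice. The main reason it gives is that "the real execution of true experiment in the field is almost impossible due to heterogeneity of the beneficiaries". It then adds a supporting argument: "The sample requirements for a DID design are smaller than other impact evaluation designs". No comparator, correlation or figure accompanies that sentence. The note to Table 2 applies the estimator widely: "the cells (a, b, c, and d) in the table can be primary and secondary outcomes indicators".

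The entry rule that fixes the baseline value of abstinence is in the Inclusion criteria: "Smoke more than 10 combustible cigarettes a day at the time of study enrollment".

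**The concern.** Whether DID saves participants depends on the outcome, on what it is compared with, and on how strongly baseline and follow-up are correlated. The protocol states the saving as a general property of DID.

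Two things are at stake. First, a reader may believe the chosen estimator brings a sample-size advantage that, for abstinence, cannot exist. Second, for CPD the trial will already hold a baseline value for each participant. DID uses that value with a fixed weight of one, where a regression would estimate the best weight. Any precision lost this way could be recovered at no cost.

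**Working it through.** **Inputs from the protocol.** Three randomised arms of 200 (Study design); entry at more than 10 cigarettes a day (Inclusion criteria); CPD and abstinence as primary outcomes (Primary outcomes); 18% versus 9%, two-sided alpha 0.05, power 0.80 (Table 1).

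**Inputs not in the protocol.** The CPD baseline–follow-up correlation r and the two SDs. The sampling section itself says information on standard deviations is lacking. Assumed ranges: r from 0.3 to 0.7, and k = SD_follow/SD_base from 0.7 to 1.5.

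**Step 1: the plan's own figure.** Its formula gives (1.96 + 0.84)² × (0.18 × 0.82 + 0.09 × 0.91)/0.09² = 7.84 × 0.2295/0.0081 = 222.1 per group, as stated. The other three source studies also reproduce: 48.8, 86.5 and 162.5 against 49, 86 and 163. The formula compares two follow-up proportions and contains no DID variance or correlation.

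**Step 2: abstinence.** All participants smoke at entry, so a = b = 0 in Table 2. The estimator reduces to d − c, which apart from its sign is the follow-up difference between arms. Estimate, variance and required size (222 per group for 18% versus 9%) are unchanged. This step needs no assumption.

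**Step 3: CPD, direction.** Per-arm variances, in large samples:

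- Follow-up only: SD_follow²
- DID (change score): SD_base² + SD_follow² − 2r·SD_base·SD_follow
- Adjusted for baseline: SD_follow²(1 − r²)

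DID minus adjusted is SD_base² − 2r·SD_base·SD_follow + r²·SD_follow² = (SD_base − r·SD_follow)². This is never negative, so DID cannot be the more precise of the two, whatever r and the SDs are. DID has smaller variance than follow-up only when r > SD_base/(2·SD_follow), which is r > 0.5 if the SDs are equal.

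**Step 4: CPD, size with equal SDs.** Relative to follow-up only, DID is 2(1 − r) and adjusted is 1 − r². Their ratio is 2/(1 + r). The size columns show the number per arm that matches 200 per arm analysed at follow-up only.

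| r | DID | Adjusted | Ratio | n per arm, DID | n per arm, adjusted |
|---|---|---|---|---|---|
| 0.3 | 1.40 | 0.91 | 1.54 | 280 | 182 |
| 0.5 | 1.00 | 0.75 | 1.33 | 200 | 150 |
| 0.7 | 0.60 | 0.51 | 1.18 | 120 | 102 |

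A simulation with 200 per arm and 3,000 replicates gave ratios of 1.52, 1.37 and 1.19, in line with these.

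**Step 5: CPD, size with unequal SDs.** Ratio = [(k² + 1 − 2rk)/k²]/(1 − r²).

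| k | r = 0.3 | r = 0.5 | r = 0.7 | DID beats follow-up only if r exceeds |
|---|---|---|---|---|
| 0.7 | 2.40 | 2.15 | 2.04 | 0.71 |
| 1.0 | 1.54 | 1.33 | 1.18 | 0.50 |
| 1.3 | 1.24 | 1.10 | 1.01 | 0.38 |
| 1.5 | 1.15 | 1.04 | 1.00 | 0.33 |

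The extremes are 2.184/0.91 = 2.40 and 0.511/0.51 = 1.002.

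**The case against.** The strongest reply is that the sentence does little work. Heterogeneity is the lead reason for DID and the sample-size remark is secondary. That is right, so the point concerns a supporting argument. Heterogeneity does not rescue the choice, however, because randomisation already deals with it between arms.

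A second reply is that the sentence compares DID with other evaluation designs, and baseline-adjusted regression is not one the protocol mentions. This stands in part. DID does need fewer participants than a follow-up-only comparison when r is high enough, and the protocol gives no figures to test the claim against propensity score matching. What fails is the unqualified generality.

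A third reply is that the CPD loss may be negligible. Entry is cut off at more than 10 a day, while follow-up will pile up at zero among quitters, so the follow-up SD may well exceed the baseline SD. At k = 1.5 and r = 0.5 the ratio is 1.04, not 1.33. This also stands: the direction is certain, the size is not.

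Finally, a change-score analysis of randomised arms is valid. That is correct; nothing here suggests bias.

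A reader might go further and infer that the sentence was used to justify 200 per arm when the first scenario in Table 1 requires 222. The documents do not support that. The 600 comes from the two-proportion formula and the rounding that follows it, in the sampling section, and deleting the sentence would change no number. The 222 also belongs to a binary outcome, for which DID loses no precision; no sample size was computed for CPD.

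**Conclusion.** The point holds as one of efficiency and of a misleading statement; the computed sample size and the validity of the estimate are not affected. For abstinence the claimed saving is exactly zero, on the protocol's own entry rule. For CPD, DID is never more precise in large samples than adjustment for baseline. Its variance is 1.18 to 1.54 times as large with equal SDs and r from 0.3 to 0.7, and about 1.00 to 2.40 times over the wider SD range. Those sizes rest on assumed values of r and the SDs. At r = 0.5 with equal SDs, 200 per arm adjusted for baseline is worth 200 × 1.33 ≈ 267 per arm under DID, but this illustrates one case and does not estimate the loss in this trial.

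**What to change.** - Delete the sentence on the sample requirements of DID.
- Analyse CPD by linear regression of follow-up CPD on randomised arm with baseline CPD as covariate, or by a repeated-measures mixed model with the same covariate.
- Analyse abstinence as the follow-up difference between arms, adjusted for baseline CPD and motivation to quit.

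The baseline survey in the Study design section already covers smoking behaviour and motivation to stop. The cost is a wording change and one model statement, with no extra participants, visits or measurements.
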